### 9.3.2 Assessment of Causality

The PI or delegated clinician must perform an evaluation of causality for each adverse event. The investigator will use clinical judgement to determine relationship to IMP, device or device deficiency.

| Causality Category | Causality category definition                                                                                                                                                               |
|--------------------|---------------------------------------------------------------------------------------------------------------------------------------------------------------------------------------------|
| Definitely         | Temporal relationship of the onset, relative to administration of the product, is reasonable and there is no other cause to explain the event, or a re-challenge (if feasible) is positive. |
| Probably           | Temporal relationship of the onset of the event, relative to the administration of the product, is reasonable and the event is more likely explained by the product than any other cause    |
| Possibly           | Temporal relationship of the onset of the event, relative to administration of the product, is reasonable but the event could have been due to another, equally likely cause.               |
| Unlikely           | Temporal relationship of the onset of the event, relative to administration of the product, is likely to have another cause which can by itself explain the occurrence of the event.        |
| Not Related        | Temporal relationship of the onset of the event, relative to administration of the product, is not reasonable or another cause can by itself explain the occurrence of the event.           |

### 9.3.3 Assessment of Seriousness

Those AEs/ARs/ADEs meeting the definition of Serious (SAE) as per section 9.1 must also be assessed for expectedness as per the Instructions for Use for the device. Each SAE must be reported to the Sponsor as per section 9.2 and 9.4.

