### 2.1.2 Risks to participant in relation to IMP/Device combination

The AeroFact-COVID™ (AF-COVID) combination product system (nebuliser) is not a marketed product in-itself.

Regarding administration of AF-COVID to intubated, mechanically ventilated adult patients, the risks are in 3 groups:

1. Risks associated with the use of the Device are controlled in the Warning Section of the Instructions for Use. (DFU. Quick start Guide and Instructions for use, page 3-4).
2. Risks associated with SF-RI 1 surfactant are risks related to bolus instillation delivery via the endotracheal tube.
3. Risks associated with the combination product:
  - Hypoventilation, hypoxemia
  - Pneumothorax (associated with treatment related changes in lung compliance)
  - Progression of COVID-19-related ARDS
  - Irritation of the airways
  - Introduction of pathogens other than COVID-19 to the respiratory tract
  - Further dissemination of COVID-19 by aerosol

These clinical risks will be properly controlled and/or mitigated relative to the device design e.g. verification testing or labelling (instructions, warnings and cautions). Furthermore, the drug delivery system will be tested for its safety following ISO and IEC standards for materials, biological and electrical safety, and electromagnetic compatibility.

Since there is no current clinical experience with AeroFact-COVID™ combination product, there are no observed expected adverse reactions that can serve the investigators as guidance for reporting serious adverse events in the clinical study. Therefore, all treatment related Serious Adverse Events (SAEs) will be considered unexpected and will be reported to the authorities as per national requirements.

Please refer to the Investigators Brochure – Reference Safety Information Section - for a detailed list of clinical hazards identified in the initial risk assessment based on the nature of the product and the target population.

There is no guarantee that adult patients exhibiting ARDS symptoms due to lung infection with SARS CoV-2 will receive direct benefit from AeroFact-COVID™. The benefits of AF-COVID may be an improvement of lung function and decreased need for escalation of respiratory support.

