### 9.3.4 Assessment of Expectedness

Since there is no current clinical *experience with AeroFact-COVID combination product*, there are **no observed expected adverse reactions** that can serve the investigators as guidance for reporting serious adverse events in the clinical study. Therefore, **all treatment related Serious Adverse Events (SAEs) will be considered unexpected** and will be reported to the authorities as per national requirements.

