## 9.4 Recording and reporting of SAEs, SARs, SUSARs, SADEs, USADEs and DD

Any **SAE** occurring from the time of **start of trial treatment** until 28 days post cessation of trial treatment must be recorded on the combined IMP/Device SAE Report Form and Device Deficiency form (if SAE is related to DD) and sent to the Sponsor ([[contact]](mailto:[contact])) and CRO ([[contact]](mailto:[contact])) **immediately or within 24 hours** of the research staff becoming aware of the event.

Any change of condition or other follow-up information should be sent to the Sponsor and CRO as soon as it is available or at least within 24 hours of the information becoming available. Events will be followed up until the event has resolved or a final outcome has been reached.

All SAEs assigned by the PI or delegate (or following central review) as suspected to be related to IMP-treatment are deemed unexpected, will be classified as SUSARs and will be subject to expedited reporting to the Medicines and Healthcare Products Regulatory Agency (MHRA) medicines sector.

For all Device Deficiencies, the investigator needs to complete the DD form and sent to the Sponsor ([[contact]](mailto:[contact])) and CRO ([[contact]](mailto:[contact])) **immediately or within 24 hours** of the research staff becoming aware of the event.

Please refer to the Safety Reporting Flowchart below.

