## 9.4 Responsibilities

### Principal Investigator (PI):

Checking for and assessing AEs when participants are admitted to hospital or return for follow-up.

1. Using medical judgement in assigning severity, seriousness, causality and expectedness as per approved IB for the trial.
2. Ensuring that all SAEs are recorded and reported to the sponsor within 24 hours of becoming aware of the event and provide further follow-up information as soon as available.
3. Ensuring that SAEs are chased with Sponsor if a record of receipt is not received within 2 working days of initial reporting.
4. Ensuring that AEs are recorded and reported to the sponsor in line with the requirements of the protocol.

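### Expectedness of serious events is set by references that do not agree; a serious event attributed to the device alone can miss three reporting and review steps

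*Protocol*

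**What the plan says.** Four references for expectedness appear in the protocol.

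- **Always unexpected if related.** Section 2.1.2 reasons that, without clinical experience of the combination, "there are no observed expected adverse reactions that can serve the investigators as guidance for reporting serious adverse events". Section 9.3.4 repeats this and concludes that "all treatment related Serious Adverse Events (SAEs) will be considered unexpected". Section 9.4 (Recording and reporting) puts the rule into operation for the medicine: SAEs suspected to be related to IMP treatment "are deemed unexpected, will be classified as SUSARs and will be subject to expedited reporting".
- **Device Instructions for Use.** Section 9.3.3 says that events meeting the definition of serious "must also be assessed for expectedness as per the Instructions for Use for the device".
- **Investigator's Brochure.** Section 9.4 (Responsibilities) gives the PI this duty: "Using medical judgement in assigning severity, seriousness, causality and expectedness as per approved IB for the trial". The chief investigator's item 2 likewise has all SAEs reviewed for expectedness against the Brochure. Section 2.1.2 says that the Brochure has a Reference Safety Information section, to which it refers the reader "for a detailed list of clinical hazards identified in the initial risk assessment".
- **Risk analysis report or Brochure, for device effects.** Section 9.1 makes a serious device effect anticipated (ASADE) if its nature, incidence, severity or outcome has been identified in either document, and unanticipated (USADE) if not.

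**The concern.** An expectedness rule should give one answer for one event. Here 9.3.4 leaves nothing to judge once an SAE is considered related, yet 9.3.3 and both investigator roles require a judgement, and they name different documents to judge against. Section 9.1 adds a further test for device effects. Nothing in the protocol says which rule prevails.

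The stake is that some steps follow only from the unexpected or unanticipated label. The combination has no prior clinical use, the trial runs at two sites (section 5), and the dose may rise after each cohort of three treated patients and two controls (section 4). If one site labels a related serious event anticipated, the ethics committee and the other site may not hear of it by the route meant for that purpose. The PI's and chief investigator's recorded expectedness may also disagree with the classification that is finally reported.

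**Working it through.** No arithmetic applies. The check has three steps.

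**Step 1: what each rule makes of the same event.** Take a serious pneumothorax judged related to treatment. Section 2.1.2 names pneumothorax as a risk of the combination.

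| Rule | Answer |
|---|---|
| 9.3.4 (and 2.1.2) | Unexpected |
| 9.4 Recording and reporting | Unexpected, SUSAR, if suspected to be related to IMP treatment |
| 9.3.3, Instructions for Use | Depends on a document not at hand |
| 9.4 Responsibilities, Brochure | Depends on a document not at hand |
| 9.1, device effects | Anticipated if identified in the risk analysis report or Brochure |

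The rules can therefore give different answers for one event.

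**Step 2: which routes use the label.**

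| Route | Trigger in the protocol | Uses the label? |
|---|---|---|
| Site to sponsor and CRO, 24 hours (9.2, 9.4) | Seriousness | No |
| SUSAR to MHRA and REC, 15 days, or 7 if fatal or life-threatening (9.4) | Suspected relation to IMP treatment; unexpectedness is deemed | No |
| SAE to MHRA devices sector, 2 or 7 calendar days (9.4, Device reporting pathways) | Seriousness; urgency sets the timeline | No |
| Daily review by the protocol team; DSMB review after every three subjects (8.7, Dosage modifications) | AE, SAE and SADE data | No |
| USADE to REC, 15 calendar days (9.4, Device reporting pathways) | Unanticipated status | Yes |
| Notification of investigators (Sponsor, item 5) | SUSAR or USADE | Yes, for device effects |
| Immediate review by the chief investigator (CI, item 3) | SUSAR or USADE | Yes, for device effects |

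**Step 3: which events reach the last three rows with an open label.** An IMP-related SAE is already a SUSAR, so items 3 and 5 apply to it and the REC is told. What remains is a serious event attributed to the device alone. Section 9.3.2 provides for that attribution, since the investigator determines the relationship to IMP, device or device deficiency. The deeming sentence in 9.4 speaks of IMP treatment and does not clearly cover it. The broader treatment-related wording of 9.3.4 may cover it, but the definition in 9.1 points the other way. If such an event is already identified in the risk analysis report or Brochure, 9.1 makes it an ASADE and all three label-dependent steps can fall away.

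**The case against.** A reader might infer that a related pneumothorax or hypoxaemia could be called expected and so drop out of expedited reporting altogether. The documents do not support that. Section 9.4 expedites every SAE suspected to be related to IMP treatment, whatever an assessor wrote about expectedness, and the devices-sector route to the MHRA carries no expectedness condition. Oversight within the trial does not depend on the label either. All SAEs reach the sponsor and CRO within 24 hours, the chief investigator's item 2 covers all SAEs, and the protocol team and DSMB see the safety data in any case. This part of the objection stands and limits the point to device-only events.

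It can also be said that identified hazards are not the same as expected reactions. If the Brochure declares no serious reaction expected, the PI and chief investigator duties agree with 9.3.4. That is fair, and without the Brochure it cannot be settled. It does not dispose of the device definition, however. Section 9.1 asks whether the effect has been identified in the risk analysis report or Brochure, not whether it is an expected reaction, so a hazard list could be enough to make an effect anticipated. Because the test also looks at incidence, severity and outcome, a listed hazard is not automatically anticipated. Nor does a Brochure without expected reactions remove the Instructions for Use step in 9.3.3.

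Nor do the documents show that the hazards listed in section 2.1.2 are the most likely serious events in this trial. They give no frequency for them.

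**Conclusion.** The inconsistency is established on the protocol's own text, and its consequence is limited. A failure of expedited reporting to the authority is not shown. Three steps are exposed: the 15-day USADE report to the REC, notification of the other site's investigators, and the chief investigator's immediate review. They are exposed only for a serious event attributed to the device alone and already identified in the risk analysis report or Brochure. In addition, expectedness recorded by the PI or chief investigator can contradict the reported classification for any related SAE.

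Two assumptions carry this: that the risk analysis report or Brochure identifies events of the kind section 2.1.2 names, and that the deeming sentence in 9.4 is read as limited to the medicine. How many events would be affected cannot be estimated from the documents. The correction is worth making because the product combination is in first use and the change is small.

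**What to change.** Reconcile the places concerned (the device definitions in 9.1, 9.3.3, 9.3.4 and both sections numbered 9.4) to the one rule that 9.3.4 already justifies.

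1. Remove the Instructions for Use expectedness step from 9.3.3.
2. Align the PI and chief investigator duties in 9.4 (Responsibilities) with 9.3.4, so that neither role makes a separate judgement of expectedness for related SAEs.
3. State in 9.3.4 and in 9.4 (Recording and reporting) that the rule covers SAEs related to the IMP, the device or both. Add that in this trial related serious device events are handled as USADEs, notwithstanding the general definition in 9.1. Without that clause the edit would create a new conflict with 9.1.
4. Keep the Brochure's Reference Safety Information section and the sponsor's annual check for updates to it, and state that it lists no expected serious reactions for reporting purposes. The hazard list then serves as information.

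The cost is wording in these sections and a matching check of the SAE form. The downside is possibly a few more expedited reports.

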### 9.3.4 Assessment of Expectedness

Since there is no current clinical *experience with AeroFact-COVID combination product*, there are **no observed expected adverse reactions** that can serve the investigators as guidance for reporting serious adverse events in the clinical study. Therefore, **all treatment related Serious Adverse Events (SAEs) will be considered unexpected** and will be reported to the authorities as per national requirements.

## 9.4 Recording and reporting of SAEs, SARs, SUSARs, SADEs, USADEs and DD

Any **SAE** occurring from the time of **start of trial treatment** until 28 days post cessation of trial treatment must be recorded on the combined IMP/Device SAE Report Form and Device Deficiency form (if SAE is related to DD) and sent to the Sponsor ([[contact]](mailto:[contact])) and CRO ([[contact]](mailto:[contact])) **immediately or within 24 hours** of the research staff becoming aware of the event.

Any change of condition or other follow-up information should be sent to the Sponsor and CRO as soon as it is available or at least within 24 hours of the information becoming available. Events will be followed up until the event has resolved or a final outcome has been reached.

All SAEs assigned by the PI or delegate (or following central review) as suspected to be related to IMP-treatment are deemed unexpected, will be classified as SUSARs and will be subject to expedited reporting to the Medicines and Healthcare Products Regulatory Agency (MHRA) medicines sector.

For all Device Deficiencies, the investigator needs to complete the DD form and sent to the Sponsor ([[contact]](mailto:[contact])) and CRO ([[contact]](mailto:[contact])) **immediately or within 24 hours** of the research staff becoming aware of the event.

Please refer to the Safety Reporting Flowchart below.

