#### 3.3.2 Secondary Endpoints

The key secondary endpoint is safety over the first 28 days after administration of surfactant assessed by:

1. Cumulative incidence of serious adverse events (SAEs and SADEs);  
Cumulative incidence of Grade 3 and 4 adverse events (AEs)  
Cumulative incidence of ADEs and  
Changes in white cell count, hemoglobin, platelets, creatinine, glucose, total bilirubin, ALT, and AST over time.

Other secondary endpoints are:

2. Change in  $\text{PaO}_2/\text{FiO}_2$  at 24 and 48 hours after study initiation
3. Change in value of Ventilation Index at 24 and 48 hours after study initiation
4. Change in pulmonary compliance ( $\text{L}/\text{cmH}_2\text{O}$ ) at 24 and 48 hours after study initiation

5. Change in PEEP requirement at 24 and 48 hours after study initiation
6. Ordinal outcome assessed daily while hospitalised and on days 15 and 28
  1. *Not hospitalised, no limitations on activities*
  2. *Not hospitalised, limitation on activities;*
  3. *Hospitalised, not requiring supplemental oxygen;*
  4. *Hospitalised, requiring supplemental oxygen;*
  5. *Hospitalised, on non-invasive ventilation or high flow oxygen devices;*
  6. *Hospitalised, on invasive mechanical ventilation or ECMO;*
  7. *Death.*
7. Duration of mechanical ventilation- Number of days on mechanical ventilation
8. Mechanical ventilator free days (VFD) at day 21
9. Length of intensive care unit stay
10. Number of days hospitalised
11. Mortality at day 28 - Date and cause of death (if applicable)

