|-----------------------------|----------------------------------------------------------------------------------------------------------------------------------------------------------------------------------------------|----------------------------------------------------------------------------------------------------------------------------------------------------------------------------------------------------------------------------------------------------------------------------------------------------------------------------------------|--------------------------------------------------------------|
|                             | Index (VI), where $VI = [RR \times (PIP - PEEP) \times PaCO_2]/1000$                                                                                                                         | hours after study initiation                                                                                                                                                                                                                                                                                                           |                                                              |
| Secondary Objectives |                                                                                                                                                                                              |                                                                                                                                                                                                                                                                                                                                        |                                                              |
| 1                           | To assess safety as judged by the frequency and severity of adverse events (AEs), Adverse Device Effects (ADEs), Serious Adverse Events (SAEs) and Serious Adverse Device Events (SADEs).    | 
Cumulative incidence of serious adverse events (SAEs) and serious adverse device events SADEs
 
Cumulative incidence of Grade 3 and 4 adverse events (AEs).
 
Cumulative incidence of ADEs.
 
Changes in white cell count, haemoglobin, platelets, creatinine, glucose, total bilirubin, ALT, and AST over time.
 | Recorded daily over the first 28 days after study initiation |

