## 9.2 Operational definitions for (S)AEs/(S)ADEs

AEs, SAEs, SUSARs, ADEs, SADEs and USADEs will be recorded and reported according to applicable trial regulations.

All adverse events that occur between informed consent and until 28 days post cessation of trial treatment must be recorded in the subject notes and in the trial CRFs.

Pre-existing conditions (as recorded at screening visit) do not qualify as adverse events unless, in the opinion of the treating clinician, have worsened since baseline.

The following pre-specified respiratory deteriorations or adverse events occurring during nebulisation and occurring within 48 hours will be recorded:

1. Increase in oxygen or ventilator requirements [increase in  $FiO_2 \geq 0.2$  or more and or increase in PEEP of  $\geq 5$  or more to maintain the targeted oxygen saturation
2. Sustained deterioration in pulmonary ventilation variables  $>10\%$  (increase in peak or mean airway pressures, decrease in tidal volume)
3. Any episodes of new cardiac arrhythmia
4. Sustained reduction in mean arterial blood pressure (MAP) of  $>10\%$  or an increase in the vasopressor dose of Norepinephrine (0.1 mcg/kg/min), Epinephrine (0.1 mcg/kg/min) or the use of additional use of other inotropes (dopamine/dobutamine/milrinone) or vasopressors (vasopressin, terlipressin, phenylephrine)
5. Sustained increase in heart rate  $>20\%$
6. New bronchospasm requiring treatment

Other respiratory deteriorations: Incidence of pneumothorax (evidence on imaging), pulmonary haemorrhage (clinical), acute lobar collapse (evidence on imaging).

All SAEs and Device Deficiencies (as per definitions) must be recorded and reported to the Sponsor ([[contact]](mailto:[contact])) and CRO ([[contact]](mailto:[contact])) immediately/within 24hrs of the site becoming aware of the event.

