### Safety

The incidence and 95% Confidence Intervals of SAEs, and Grade 3 or 4 AEs will be summarized by randomization group over the first 24 hours, and throughout the study. The number and percentage of participants with AEs will be summarized by Medical Dictionary for Regulatory Activities (MedDRA) system organ class (SOC) and preferred term (PT). Additional summaries will present the number and percentage of participants with adverse events by intensity and by relationship to surfactant treatment. Summary statistics will be generated for raw laboratory safety tests, as well as for any changes from baseline, as deemed clinically appropriate.

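### Sections 3.3.2, 3.4, 9.2 and 9.4 give conflicting safety windows, and those tied to treatment or nebulisation have no equivalent for the 8 controls

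*Protocol*

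**What the plan says.** The protocol sets the safety window in four places.

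- **Section 9.4 (recording and reporting)** covers any SAE "occurring from the time of start of trial treatment until 28 days post cessation of trial treatment must be recorded".
- **Section 9.2** has a different start for AEs: "All adverse events that occur between informed consent and until 28 days post cessation of trial treatment must be recorded". A separate sentence there sets no start for serious events: "All SAEs and Device Deficiencies (as per definitions) must be recorded and reported to the Sponsor".
- **Section 3.3.2** ties the endpoint to the drug: "The key secondary endpoint is safety over the first 28 days after administration of surfactant assessed by" SAEs and SADEs, Grade 3 and 4 AEs, ADEs and laboratory changes.
- **Table 3.4** gives the same outcomes another origin: "Recorded daily over the first 28 days after study initiation".

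Section 9.2 also lists six respiratory and haemodynamic deteriorations, introduced as "adverse events occurring during nebulisation and occurring within 48 hours will be recorded". It does not say what the 48 hours are counted from.

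In section 10 (Safety), the incidence of SAEs and of Grade 3 or 4 AEs, with 95% confidence intervals, "will be summarized by randomization group over the first 24 hours, and throughout the study". Section 4 puts 2 controls in each of 4 cohorts and says that their protocol differs from the treated arm only in having no surfactant nebulisation.

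**The concern.** These sections define the same safety data, yet they differ in start, in end and in the event that anchors them. Section 9.3.3 sends the site to both 9.2 and 9.4 for SAE reporting, so a site must follow two sections with different starts.

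An anchor on treatment or nebulisation exists in one arm only. A site that applies those sentences literally will look for events over a defined period in treated patients and over an undefined one in controls. Rates by arm then partly reflect the recording rule. Section 10 presents such rates with confidence intervals, and section 4 uses reported adverse events when deciding whether to change dose between cohorts. Even a descriptive comparison needs the same ascertainment in both arms.

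A smaller matter is the time before the first dose. Two study procedures take place then in treated patients, and 9.4 taken by itself starts too late to cover them.

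**Working it through.** **1. Patients affected.** Section 4: 4 cohorts x 2 = 8 controls, which agrees with the stated total of 8. Treated: 4 x 3 = 12. All patients: 20. Controls are 8/20 = 40%.

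**2. The windows side by side.**

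| Source | Start | End | Defined for controls? |
|---|---|---|---|
| 9.4, SAEs | first treatment | 28 days after treatment ends | neither start nor end |
| 9.2, AEs | consent | 28 days after treatment ends | start only |
| 9.2, SAE sentence | not stated | not stated | no limit by arm |
| 3.3.2, endpoint | surfactant | 28 days later | neither start nor end |
| 3.4, endpoint | study initiation | 28 days later | yes |
| 9.2, deterioration list | nebulisation, and 48 h from an unstated origin | as start | not by the nebulisation wording |

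Section 4 does mention a matching time for controls, but only for the review after each cohort. No safety window uses it.

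**3. End date.** Last planned dose at 24 h + 28 days = Day 29. If dosing stops after the dose at 0 h, the end is Day 28. Appendix 1 stops at Day 28. The difference is one day and minor in itself.

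**4. Before the first dose.** Section 7.7 starts the 3-hour choline infusion in the stabilisation period before dose 1. Section 7.11 allows the baseline aspirate, with 20-50 mL saline, up to 30 minutes before dose 1. Both lie outside the 9.4 window and inside the 9.2 AE window. Giving controls a matching time zero in 9.4 would not make the arms equal. Section 7.11 (item 5) gives controls the infusion at the time that corresponds to surfactant, so it would fall inside their window but outside that of treated patients.

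**5. The deterioration list.** Minimum nebulisation time = vials x 2.2 mL / 0.3 mL/min (volume from 8.7, maximum rate from 8.4):

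- 30 vials: 30 x 2.2 / 0.3 = 220 min = 3.7 h
- 50 vials: 6.1 h
- 70 vials: 8.6 h
- 90 vials: 90 x 2.2 / 0.3 = 660 min = 11.0 h
- controls: 0 h

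The protocol gives no event rate, so the 48-hour risk p is an assumption: 25%, 50% or 75%, equal in both arms, with constant hazard.

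*Narrow reading (the event must occur during nebulisation, in both arms).* The chance of a recorded event in t hours is 1 - (1 - p)^(t/48). Expected recorded treated patients = 3 x the sum over the four cohorts.

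| p | Chance by cohort 1-4 | Treated recorded, of 12 | Controls recorded, of 8 |
|---|---|---|---|
| 25% | 2.2, 3.6, 5.0, 6.4% | 0.5 | 0 |
| 50% | 5.2, 8.4, 11.6, 14.7% | 1.2 | 0 |
| 75% | 10.0, 16.2, 21.9, 27.2% | 2.3 | 0 |

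The control count is 0 of 8 by construction (95% CI 0 to 36.9%).

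*Wide reading (anything within 48 h counts, in both arms).* At p = 50% the expected counts are 6 of 12 and 4 of 8. The arms agree, provided that the 48 hours have an origin in controls, which the text does not supply.

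**6. Observation frequency.** Section 7.7 adds readings between vials: 10 - 1 = 9 or 30 - 1 = 29 intervals per dose, in treated patients only.

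**The case against.** The strongest reply is that the document as a whole already covers both arms. Table 3.4 has a usable origin. Appendix 1 marks adverse event assessments from D0 to D28 and restricts only the nebuliser and surfactant rows to the treated arm. Section 9.9 records adverse events throughout participation, and 9.5 has every death reported. This stands. The missing window for controls is a fault of particular sentences, and their data would still be collected.

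A reader might infer that SAEs from procedures before the first dose escape 24-hour reporting. The documents do not support that. Section 9.2 records AEs from consent and requires all SAEs within 24 hours with no start limit, and 9.3.3 points to 9.2 together with 9.4. What remains is a contradiction between two sections that sites must both follow.

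A reader might also infer a false excess of about 40 percentage points in treated patients, by assuming a 40% risk in both arms and counting no controls. That figure applies the wide 48-hour reading to treated patients and the narrow nebulisation reading to controls. Used consistently, neither reading gives it. Nor would it be an excess in a specified endpoint: the list is in neither the key secondary endpoint nor the incidence summaries of section 10. A control with a new arrhythmia or bronchospasm can still be entered as an ordinary AE.

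Finally, section 8.7 (Dosage modifications) says that safety will not be formally compared between arms, so calling the rates not comparable is too strong. Between-vial readings are also monitoring and not events, and several list items require a sustained change. Both points limit the consequence but leave the conflicting text in place.

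**Conclusion.** The point holds as an internal contradiction with a limited consequence. Four sections give different safety windows, and those tied to treatment or nebulisation are undefined for 8 of 20 patients. The risk is unequal ascertainment in descriptive rates by arm, and inconsistent SAE reporting before the first dose.

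For SAEs and Grade 3 or 4 AEs the effect should be small if sites follow 9.2, table 3.4 and Appendix 1. It is greatest for the deterioration list. On its narrow reading, controls score zero whatever happens to them, against roughly 0.5 to 2.3 expected among 12 treated patients. That range rests on an assumed equal 48-hour risk of 25-75%, constant hazard and the maximum nebulisation rate; slower delivery would lengthen the treated window.

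**What to change.** Reconcile 3.3.2, 3.4, 9.2 and 9.4 to one window for both arms.

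- **AEs and SAEs:** from legal-representative assent to Day 28 after study initiation. State what study initiation means in each arm, with an equivalent time zero for controls.
- **Pre-specified deteriorations:** from 0 to 48 h after study initiation in both arms, at the observation times that both arms share.
- **Events seen only on between-vial readings:** flag them and report them separately as treated-arm tolerability.

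The cost is protocol wording and eCRF date logic, plus some extra SAE forms for controls and for events before the first dose. No visits or procedures are added, because the adverse event schedule in Appendix 1 already applies to both arms.
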